## Abstract

**Introduction:**

Tourette syndrome (TS) and chronic motor or vocal tic disorder (CTD) are neurodevelopmental disorders associated with functional impairment and reduced quality of life. Behavioral therapy (BT) is an effective treatment, but lack of experienced practitioners makes it hard for patients to receive appropriate help. One approach to bridge the gap between demand and availability is to offer the treatment remotely over the internet with minimal support from a therapist.

**Methods:**

This single-blind randomized controlled superiority trial including 110 participants will compare internet-delivered BT (I-BT) primarily consisting of exposure and response prevention (ERP) to a control condition consisting of internet-delivered general psychological support. The primary aim of the trial is to evaluate whether ERP-based I-BT is superior to the control condition in reducing TS/CTD symptoms. The primary outcome measure is the Yale Global Tic Severity Scale - Total Tic Severity score administered by blinded raters at primary endpoint 11 weeks after the treatment start. Secondary endpoints occur at week 23 and 14 months after the treatment start, and the secondary outcomes include tic-related impairment, rates of responders, self-rated tic severity, symptoms of depression, quality of life and cost-effectiveness. Data on dropout rates and adverse events is also collected.

**Discussion:**

This is the first randomized controlled trial to evaluate therapist-guided ERP-based I-BT for adults with TS/CTD. The study has been approved by the Swedish Ethical Review Authority (EPM 2023-06541-01). The hypotheses were pre-registered before the start of the data collection. Results from all analyses will be reported according to the Consolidated Standards of Reporting Trials statement for non-pharmacological trials (CONSORT) and Consolidated Health Economic Evaluation Reporting Standards (CHEERS). The participants in the control condition will have the opportunity to receive I-BT after the data from the first follow-up is collected. The study will be published in open access and the results will be shared with service user organizations. At the moment of submission, the study has recruited 87 out of 110 planned participants and the recruitment is expected to be completed in February 2025.

**Trial registration:**

Open Science Framework: https://osf.io/cq97b/ (uploaded 31/01/2024); Clinicaltrials.gov: NCT06271083 (submitted 14/02/2024).

## Introduction

1

Tourette syndrome (TS) and chronic motor or vocal tic disorder (CTD) are neurodevelopmental conditions that originate and typically peak in childhood (1), but about 20% of patients seem to present with the symptoms beyond their teenage years (2, 3). TS is characterized by both motor and vocal tics for at least one year, while CTD involves either motor or vocal tics also lasting at least one year (1). Both conditions are associated with reduced quality of life, lower educational attainment, risk of other psychiatric and somatic conditions, and increased mortality rates (3–10).

The most common pharmacological treatment for TS/CTD is antipsychotic medication, which is associated with substantial side effects (11). Behavior therapy (BT) is a non-pharmacological treatment option aimed at teaching individuals to better manage their tics (12). BT is an effective treatment (13–16), but is not always available due to a lack of experienced practitioners.

One approach to increase treatment availability is to offer BT online instead of in-person (17). Internet-delivered BT (I-BT) includes the same treatment content but is delivered through a secure online platform. Patients work with self-help materials and assignments and communicate with a therapist via the platform. Research shows that self-help-based I-BT can be provided to adults with TS/CTD (18). Therapist-supported I-BT using exposure and response prevention (ERP) techniques has been successfully provided to children and adolescents in two large randomized controlled trials (19, 20) with one trial showing significant reductions in tic severity compared to an active control group (19), and the second trial showing significant reductions in both groups with no between-group effect (20). Our research group recently conducted a feasibility trial of internet-delivered ERP for adults (*n* = 31) with TS/CTD (21). The treatment was deemed both feasible and safe. Additionally, preliminary efficacy results showed a significant within-group tic severity reduction, with an effect size of Cohen's d = 0.49.

The primary aim of the study is to investigate whether guided internet-delivered ERP-based BT is superior to an active control condition consisting of guided internet-delivered general psychological support in reducing TS/CTD symptoms. We hypothesize that, compared to the control group, participants in the treatment group will show greater reduction in tic severity, as measured with Yale Global Tic Severity Scale - Total Tic Severity subscale (YGTSS-TTS) (22) at the primary endpoint (post treatment or week 11 after treatment start).

The secondary aim at the primary endpoint (week 11 after the start of the treatment) is to compare the two arms regarding:
(1)Tic-related impairment(2)Rates of responders(3)Self-rated tic severity(4)Symptoms of depression(5)Quality of life(6)Cost-effectivenessThe third aim is to evaluate long-term maintenance of gains. We hypothesize that the intervention condition will be superior to the control condition at week 23 after the treatment start (better response, less severe symptoms, higher quality of life) regarding all outcome measures and that the results will be maintained in the intervention group at the 14-month follow-up. The fourth aim is to evaluate the cost-effectiveness of the intervention from the healthcare organization payer perspective, the healthcare system perspective, and the societal perspective.

## Methods and analysis

2

### Trial design

2.1

A parallel group randomized (1:1) controlled superiority trial (RCT) will be carried out at Karolinska Institutet in Stockholm, Sweden. The study will be conducted in Swedish and will include a total of 110 adult participants with TS/CTD. The study will be conducted according to the Declaration of Helsinki and relevant parts of ICH E6 Good Clinical Practice (GCP). The Consolidated Standards of Reporting Trials (CONSORT) flow chart for the trial is shown in Figure 1. Both the outcome measures and the treatment will be administered via a secure online treatment platform (BASS4) requiring two-step authentication, run by the Karolinska Institutet eHealth Core Facility. Prior to the start of recruitment, the trial was approved by the Swedish Ethical Review Authority (EPM 2023-06541-01) and pre-registered at Open Science Framework, osf.io (https://osf.io/cq97b/). The trial was registered at ClinicalTrials.gov (NCT06271083) at the very start of recruitment. Potential protocol modifications will be described in detail on osf.io, ClinicalTrials.gov, and, if required, amendments will be submitted to the Swedish Ethical Review Authority.

**Figure 1 F1:**
[figure not shown]
CONSORT flow chart over the trial recruitment and treatment process.

### Participants

2.2

Eligibility criteria for the participants are listed in Table 1. The participants will be recruited nationally by means of advertisement in social and regular media (online and printed copies) and by spreading information via psychiatric and neurological clinics and service user organizations across Sweden. The advertisements will guide the prospective participants to the study website (ticsstudien.se) where more detailed information about the study will be provided and the visitor will be encouraged to proceed to the treatment platform for registration. During the registration procedure, the prospective participants will be provided necessary practical information about the project. Thereafter, if they are still interested in participating, they will provide digital consent for study participation, identify themselves with two-step authentication by receiving a text message to their phone number and e-mail address, create an account at the treatment platform, and fill out a preliminary screening form focused on the nature and severity of their tics, the eligibility criteria, and sociodemographic information. Potentially eligible participants will undergo a psychiatric assessment via video-conferencing software or telephone to check the eligibility criteria, collect clinician-administered measurements, and assess psychiatric comorbidities. Eligible participants will be included in the trial, randomized, and enrolled within two weeks after the assessment of pre-treatment tic severity with the YGTSS (if more than two weeks pass from the date of pre-treatment YGTSS to the start of the treatment, the pre-treatment YGTSS will be re-administered).

**Table 1 T1:** Overview of eligibility criteria.

Type of eligibility criteria	Eligibility criteria
Inclusion criteria	≥18 years of age.
	Primary diagnosis of TS/CTD, according to DSM-5 criteria.
	Provided digital informed consent.
	A Total Tic Severity Score (TTS) of >15, or >10 for individuals with motor or vocal tics only, in the past week, as measured by the Yale Global Tic Severity Scale (YGTSS).
	Willing and able to follow the study procedures and participate in the 10-week treatment program.
	Fluent in Swedish.
	Regular access to a computer connected to the internet, sufficient technical skills to use the treatment platform, as well as a mobile phone to receive text messages.
Exclusion criteria	Ongoing or planned psychological treatment for TS/CTD.^a^
	Previous BT for TS/CTD of a minimum of 8 sessions with a qualified therapist within 12 months prior to assessment.^a^
	Adjustment of medication for TS/CTD within the last two months prior to assessment.^a^
	Severe psychiatric comorbidities such as organic brain disorders, bipolar disorder, ongoing psychosis, anorexia nervosa or substance use disorders that may interfere with the treatment for TS/CTD.^a^
	Acute psychiatric problems such as severe depression or suicidal risk needing immediate psychiatric care.
	Severe tics causing immediate risk to the participants themselves or to others and requiring urgent medical attention.

DSM-5, diagnostic and statistical manual of mental disorders, fifth edition; TS/CTD, Tourette syndrome/ chronic tic disorder; YGTSS, Yale Global Tic Severity Scale; YGTSS-TTS, Yale Global Tic Severity Scale—Total Tic Severity subscale.

^a^
These criteria are selected for exclusion as these factors can interfere with the treatment.

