The primary outcome measure will be the YGTSS-TTS (22), administered by a clinician blinded to the randomization condition. The raters will be psychiatrists or psychiatry residents, clinical psychologists, psychologists under training or psychology students receiving supervision. The raters will receive training in administering the YGTSS and participate in at least two test ratings with subsequent supervision before they are allowed to conduct assessments in the trial. Co-ratings will be arranged every 6 months for the active raters during the data collection period. Data on inter-rater reliability will be reported.

Secondary clinician-rated outcome measures will be the YGTSS-Impairment, as well as the Clinical Global Impression—Severity and Improvement (CGI-S and CGI-I, the latter not administered at pre-treatment) (23). The clinicians will receive training in administering the CGI that will be repeated every 6 months. Participants that are rated as “much improved” or “very much improved” on the CGI-I will be classified as treatment responders (24). If the participant keeps the responder status at subsequent follow-ups, they will be classified as long-term responders at that follow-up.

Self-rated tic-specific outcome measures will be the Adult Tic Questionnaire (ATQ) (also administered weekly) (25), the Gilles de la Tourette Syndrome—Quality of Life Scale (GTS-QoL) (26), and the Work and Social Adjustment Scale (WSAS) (27) adapted for TS/CTD by the research team. General quality of life will be measured using the Assessment of Quality of Life—6 Dimensions (AQoL-6D) (28), and these scores will be used in the health-utility analysis (see below). Symptoms of depression will be assessed using Montgomery-Asberg Depression Rating Scale—Self-report (MADRS-S) (29) (also administered at week 3 and 7). The self-reported Treatment Inventory of Costs in Patients with psychiatric disorders (TIC-P) will be administered to measure health-related costs (30).

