### Sample size

2.5

The within-group effect size in the feasibility trial was Cohen's d = 0.49 (21). As tic severity is known to fluctuate over time, we expect a certain amount of improvement in the control condition. However, we do not expect it to be as large as in the two previous ERP-based I-BT studies in children (19, 20), because the control group in those studies was much more potent. Furthermore, the participants in our previous adult pilot trial improved as much as the participants in a previous adult trial (18), but their pre-treatment tic severity was unexpectedly low, making the overall pre-to-post-treatment effects small. In the current trial, we expect the participants to have a more representative pre-treatment tic severity and their improvement to the primary endpoint is expected to be larger. In sum, we assume the between-group effect-size measured with Cohen's d to be around 0.5. With *n* = 50 participants in each group we will achieve 80% power to detect the effect of between-group Cohen's d = 0.5 (one-tailed test). A total sample size of *n* = 110 will allow for 10% drop-out rate.

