### Randomization and blinding

2.6

The participants will be starting treatment in cohorts. Every time a cohort is ready to start, the online service random.org will be used to create a randomized list of the participants included into the cohort. The list will be emailed to a person not associated with the research group with the instruction to choose the following: (1) where an imaginary line dividing the cohort into two approximately equal groups should be drawn, and (2) whether the group above the line should be marked with “I” (meaning intervention) or “K” (meaning control). The outcome assessors will be blinded to the allocation of the participants, and they will be asked to guess the allocation after each assessment. The frequency of correct guesses will be reported as a measure of blinding integrity.

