### Statistical methods

2.7

The significance level for all statistical tests will be *α* = 0.05. For all scale level measures, Cohen's d will be used as a measure of effect size. Odds ratios will be reported for categorical variables. Confidence intervals (95%) will be reported for all estimated measures.

The intention-to-treat approach to the analysis population will be applied in all cases unless specified otherwise. In case more than 10% of the data is missing, maximum likelihood imputations will be performed based on demographical data and the scores from the pretreatment assessment. The between-group differences at week 11 (primary endpoint) for the primary (YGTSS-TTS) and secondary outcome measures, an analysis of covariance (ANCOVA) with pre-score of the measure as covariate will be calculated. For ATQ and WSAS that are collected weekly, mixed effect models will be applied with random intercept and random slope. Chi squared tests will be calculated to explore the between-group differences in proportions of responders and long-term responders at all endpoints.

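### The primary ANCOVA of YGTSS-TTS adjusts only for the pre-score; adding tic type, which the entry rule already distinguishes, is a low-cost and probably small gain in precision

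*Protocol article*

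**What the plan says.** - **Population.** The Introduction separates the two diagnoses: "TS is characterized by both motor and vocal tics for at least one year, while CTD involves either motor or vocal tics". Both are enrolled.
- **Entry.** Section 2.2, Table 1, requires "A Total Tic Severity Score (TTS) of >15, or >10 for individuals with motor or vocal tics only, in the past week".
- **Outcome.** Section 2.4 applies one total to everyone: "The primary outcome measure will be the YGTSS-TTS (22), administered by a clinician blinded to the randomization condition".
- **Analysis.** For the week-11 comparison, section 2.7 states that "an analysis of covariance (ANCOVA) with pre-score of the measure as covariate will be calculated". No other covariate is named.
- **Allocation.** Under section 2.6, "the online service random.org will be used to create a randomized list of the participants included into the cohort", and the list is then cut into two roughly equal parts. No balancing on tic type is described.
- **Planning.** Section 2.5 bases 50 per group on d = 0.5, one-tailed, with 80% power, and raises the total to 110 for 10% drop-out.

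**The concern.** The plan treats tic type as relevant to the score at entry, since it sets a lower floor for people with one type, but drops the distinction in the analysis. The pre-score carries much of any level difference, though not necessarily all of it. A pooled slope below 1 predicts that a low scorer moves toward the overall mean. If single-type participants instead regress toward a lower mean of their own, part of the difference between types is not predicted by the pre-score and stays in the residual.

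What is at stake is the width of the confidence interval for the primary comparison. Tic type is known for every participant before randomisation, so any such variance could be removed at almost no cost.

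**Working it through.** **The plan's own figure.** For two means, n per group = 2(1.645 + 0.842)² / 0.5² = 49.5, so 50, as stated. With 10% drop-out, 110 × 0.9 = 99 remain and power is 0.800. Dividing 100 by 0.9 and rounding up to an even total gives 112, within 2 of the stated 110. The figure reproduces. It rests on an unadjusted comparison and takes no credit for the pre-score.

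**Inputs.** The documents give the two floors (above 15 and above 10, so 5 points apart) and the covariate set. They do not give the following, which are assumed:
- p, the share of single-type participants: 0.10–0.20
- Δ, the mean gap between types, equal before treatment and at week 11: 5–10 points
- within-type SD: 6 (variance 36)
- r, the within-type pre-post correlation: 0.5–0.7

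**Formulas.**
- Between-type variance: B = p(1 − p)Δ²
- Pooled slope: b = (36r + B)/(36 + B)
- Residual variance, pre-score only: (36 + B)(1 − b²)
- Residual variance, pre-score plus tic type: 36(1 − r²)

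**Results.**

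| Case | p | Δ | r | B | b | Pre-score only | Plus tic type | Reduction |
|---|---|---|---|---|---|---|---|---|
| Low | 0.10 | 5 | 0.7 | 2.25 | 0.718 | 18.55 | 18.36 | 1.0% |
| Middle | 0.15 | 8 | 0.6 | 8.16 | 0.674 | 24.10 | 23.04 | 4.4% |
| Gap equal to floors, top | 0.20 | 5 | 0.5 | 4.00 | 0.550 | 27.90 | 27.00 | 3.2% |
| High | 0.20 | 10 | 0.5 | 16.00 | 0.654 | 29.77 | 27.00 | 9.3% |

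In the middle case the part of the gap that the pre-score leaves unexplained is 8 × (1 − 0.674) = 2.6 points. The interval narrows by 1 − √(1 − 0.044) = 2.2%.

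**Cost of the extra term.** With 99 analysed, residual degrees of freedom fall from 96 to 95, and the variance of the treatment estimate rises by about 1/95, or 1.1%. Net of that:
- low: 0.990 × 1.011 ≈ 1.00, no gain
- middle: 0.956 × 1.011 = 0.966, about 3%
- high: 0.907 × 1.011 = 0.917, about 8%

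**Wider assumptions.** With p 0.05–0.30, a gap of 0.5–2 within-type SDs and r 0.5–0.8, the ratio of the two residual variances runs from 1.00 to 1.15. A simulation of motor and vocal component scores under the two entry floors, with assumed means and SDs, gave 1.02 to 1.15.

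**Power.** Take 50 per group and d = 0.5 on the total SD, with p 0.1–0.3, a gap of 1–2 SDs and r 0.5–0.7. The pre-score ANCOVA alone then has one-sided power of at least 0.908. Adding tic type gains about 0.1 to 1.4 percentage points one-sided and at most about 2.4 two-sided. For example, with p = 0.10, a gap of 1 SD and r = 0.6, one-sided power moves from 0.943 to 0.947.

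**The case against.** The strongest reply is that nothing here is an error. ANCOVA on the pre-score is a standard primary analysis, and under randomisation leaving out a second prognostic factor neither biases the effect nor invalidates its standard error. That stands, and it is why this is a suggested improvement and not a correction.

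The second reply is that the mechanism is assumed. Two floors show that lower scores are admitted. They do not show how far apart the group means are, how many single-type participants there are, or whether a gap remains at a given pre-score. If the week-11 gap is just what the pooled slope predicts, the loss is zero. This also stands. The only separation in the documents is the 5 points between the floors, and at that gap the reduction is 1.0–3.2%; the 9.3% needs twice as much.

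The third is that an analysis plan not shown may add covariates. This carries less weight, because the article itself names the covariate for this analysis.

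A reader might also infer that a chance imbalance in tic type is a separate harm. It is not: the standard error already allows for it. In the middle case with 50 per arm, a one-SD imbalance is √(0.15 × 0.85 × 2/50) = 7 percentage points. Multiplied by 2.6 points, that shifts the estimate by about 0.2, against a standard error of √(24.10 × 2/50) = 0.98.

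Finally, diagnosis is not an exact stand-in for the entry category. TS and CTD are defined by tics over at least a year, while the entry score refers to the past week, so the covariate needs a stated definition.

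**Conclusion.** The point holds as a minor, optional refinement. The plan separates participants by tic type at entry, pools them on one total, and adjusts only for the pre-score. If single-type participants keep a lower mean than the pooled slope predicts, adding tic type would remove about 1–9% of residual variance under the main assumptions (4.4% in the middle case), before a cost of about 1% for the lost degree of freedom. These figures depend on a share, gap, SD and correlation that the documents do not give, so the actual size cannot be derived from them.

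A stronger reading, that the primary result would be biased or the trial underpowered, is not supported. The planned 50 per group reproduces without any covariate, and in every scenario of the power grid the pre-score ANCOVA exceeds the planned 80%.

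**What to change.** In section 2.7, add tic type as a fixed covariate beside the pre-score in the week-11 ANCOVA of YGTSS-TTS and in later between-group comparisons of YGTSS-TTS. Define it by the Table 1 category that applies at the pre-treatment YGTSS supplying the pre-score: both motor and vocal tics, or one type only. This settles any mismatch between diagnosis and current presentation.

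The cost is one sentence and one degree of freedom, with no new data collection. It should be fixed before data analysis starts, which section 5 places after the last primary-endpoint data in July 2025, and posted through the routes that section 2.1 gives for protocol modifications. Fixing it beforehand also avoids a choice made after seeing how tic type fell between the arms.

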### Interventions

2.3

#### Intervention condition: internet-delivered exposure with response prevention

2.3.1

The active intervention will contain eight chapters with homework assignments after each chapter, as well as working sheets for the participants to register and monitor their activity during the treatment. The participants will work with their treatment for 10 weeks, communicating with their therapists via asynchronous written messages in the platform. On the first day of the treatment, the participants in both intervention and control conditions will be greeted by their therapist via a message sent on the treatment platform. The therapists will introduce themselves, inform the participants about the outline of the treatment, and encourage them to start working with the treatment content immediately. The first two chapters of the treatment will be available to the participants from the start. The participants will be encouraged to work with one treatment chapter per week and the following chapter will be opened by the therapist when the previous week's homework is reviewed. The therapist's role will be to encourage the participants’ activity in the treatment and follow up on inactivity, problem solve and follow up on potential safety issues when necessary.

During the treatment, participants will receive information about tics and ERP, the central component of the intervention (see Table 2 for an overview of the ERP condition). Continuously throughout the treatment, participants will work with exposing themselves to situations that trigger their premonitory urges and practice suppressing their tics. They will learn different strategies to provoke their premonitory urges to make suppression of their tics more challenging and gradually increase the time they can suppress the tics. A central tool in the treatment will be the Ticstimer, a worksheet where participants will continuously record their ERP practice and the time they manage to suppress tics. The participants will be encouraged to work with the Ticstimer daily. Additionally, the treatment will include an introduction to habit reversal training (HRT) which is another BT-strategy, to give the participants and therapists a broader range of tools and make the treatment more suitable for regular psychiatric settings where clinicians appreciate being able to offer a range of evidence-based techniques. The treatment will include one scheduled phone call around the time the participant received the rationale for the ERP and is about to start their practice, to maximize the chance for the first practice to align with the rationale.

**Table 2 T2:** Overview of the active condition.

Chapter 1—Introduction. Provides practical information about the treatment (length, homework assignments, therapist support), and introduces the psychological model for maintenance of tics.
Chapter 2—Register the urges. Introduces the concept of premonitory urges and encourages the participants to start registering the urges as a part of their training.
Chapter 3—Exposure with response prevention. Introduces the participants to exposure and response prevention and encourages them to start using the Ticstimer.
Chapter 4—Proactive exposure Part 1. Encourages the participants to expose themselves to more challenging situations to provoke tics and try to practice suppressing tics.
Chapter 5—Proactive exposure Part 2. The participants are encouraged to get more creative to increase the difficulty level of the exercise, for example by inducing tics and then trying to interrupt them. Habit reversal strategies are introduced.
Chapter 6—Proactive exposure Part 3. The level of difficulty increases even further, as the participants are encouraged to combine different exercises and minimize avoidance of triggering situations in their everyday life.
Chapter 7—Summary of the treatment. Summarizes the core components of the treatment.
Chapter 8—Planning forward. Planning for continued work and relapse prevention.

